### Safety assessment

The following safety indicators will be measured before the study and at the end of each period (including week 8, week 16, week 24, week 32, week 40, and week 48):
Laboratory tests, including routine blood tests (white blood cell count, total number of neutrophils, total number of lymphocytes, total number of monocytes, total number of eosinophils, total basophils, percentage of neutrophils, lymphocyte percentage, percentage of monocytes, eosinophil percentage, basophil percentage, total number of red cells, haemoglobin volume, erythrocyte specific volume, mean erythrocyte volume, mean erythrocyte haemoglobin content, mean erythrocyte haemoglobin concentration, erythrocyte distribution width, total platelet count, mean platelet volume, platelet distribution width, and specific platelet volume), routine urine tests (urine specific gravity, uric acid alkalinity, urine leukocyte lipase, nitrite, urine protein, urine glucose, urine ketone body, uric bravery former, uric bilirubin, occult blood, white blood cell count, red blood cell count, epithelial cells, crystallisation, small-round-cell lipids, trichomonad fungus, tube type, and amorphous salt crystallisation), liver function tests (alanine transaminase, glutamyl transpeptidase), kidney function tests (serum creatinine), and blood lipidsVital signs including blood pressure, respiration rate, heart rate, body temperature, 12-lead electrocardiogram, and physical examinationAll adverse events occurring during the study, including toxicities and side effects, such as rash, gastrointestinal discomfort (abdominal pain, nausea, and vomiting), drug allergies, liver damage, and renal failure, will be reported and recorded in the case report form (CRF) in detail

### Sample size

Based on published data [20], whose primary outcome was the VAS score of mucus in the stool, the standard deviation of self-efficacy was 0.8, and the difference value of efficacy between the two groups was 0.7. We assume that there is no difference in efficacy between each patient. Assuming a two-sided significance level of 0.05 and power of 80% (*α* = 0.05, *β* = 0.2), the sample size is calculated as 8 (fixed model) [29]. Considering a 20% loss to follow-up, the sample size was 10 cases.

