### Rationale for using *N*-of-1 trials

A series of *N*-of-1 trials was chosen for the following reasons:
UC is characterised by repeated relapse and remission [1]. A realistic treatment approach is to maintain remission for a long period after remission induction [1]. Patients need personalised treatment to alleviate prolonged suffering. UC meets the required conditions of *N*-of-1 trialsRCTs are not suitable for all diseases and treatments. *N*-of-1 trials can be considered for nonprogressive chronic disease [24, 25]. The *N*-of-1 trial is designed for a single patient or a series of individual patients. Multiple randomised crossover trials are alternated between the intervention period and the control period [26, 27]. *N*-of-1 trials have been placed at the pinnacle of the evidence hierarchy by the Oxford Centre for Evidence-Based Medicine, with the systematic review of RCTs being in second place [28]. Compared with RCTs or crossover trials, *N*-of-1 trials have higher power and require smaller sample sizes [29]*N*-of-1 trials meet the characteristics of syndrome differentiation and the individual medical interventions in TCM. Different interventions can be set up for each patient, and this design can provide a more flexible clinical trial design for TCM

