### Statistical methods

All data will be recorded and collected on the CRFs by the researchers. The data will be input using EpiData 3.0 (EpiData Association, Odense, Denmark). To ensure the accuracy and integrity of the data, double data entry and proofreading will be performed by two independent researchers.

R software (version 3.6.2) will be utilised for the statistical analysis. A *P* value ≤ 0.05 will be considered statistically significant. For the quantitative indicators, the mean and standard deviation or the median and interquartile range will be calculated. Descriptive statistics will be used to summarise the demographic characteristics of the participants, including age, sex, and extent of UC.

For the individual *N*-of-1 trials, paired *t* tests or Wilcoxon signed-rank tests will be used to compare the efficacy (including the VAS for diarrhoea, abdominal pain, mucus in the stool, and bloody purulent stool, as well as all the QOL scores) of modified SJZD with that of mesalazine. For individual patient reports, the VAS for diarrhoea, abdominal pain, mucus in the stool, and bloody purulent stool, as well as all the QOL scores and safety indicators reported, will be described, as will whether the efficacy is within the range of significant improvement.

To synthesise the data from the *N*-of-1 trials from all patients (including the VAS for diarrhoea, abdominal pain, mucus in the stool, and bloody purulent stool, as well as all the QOL scores), a paired *t* test was used for the analysis. Considering the correlated data structure, we also used a mixed model. The equation for the mixed model is as follows [34]:

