1$$ {\displaystyle \begin{array}{l}{Y}_i={X}_i{\theta}_i+{\varepsilon}_i\kern0.5em \mathrm{with}\kern0.5em {\varepsilon}_i\sim N\left(0,{\Sigma}_i\right)\\ {}{\theta}_i\sim N\left(\theta, D\right)\end{array}} $$where *Y*_*i*_ = (*Y*_*i1*_, *Y*_*i2*_, …, *Y*_*ij*_) denotes the *i*-th (*i* = 1, 2, …, *n*) subject’s response value for the *j*-th (*j* = 1, 2, …6) period; *θ*_*i*_ follows a multivariate normal distribution with mean *θ* and a covariance matrix *D*. *θ*_*i*_ contains treatment effect (μ_i_) between mesalazine and modified SJZD. When *μ*_*i*_ is same for each patient (*μ*_*i*_ *= μ*), it is a fixed effect. If *μ*_*i*_ varies across different patients, it is a random effect. Some covariance structures for the random error are assumed, including: (1) compound symmetry (common variance across patients with uncorrelated and identically distributed errors), (2) first-order autoregressive, and (3) unstructured: which may be overparameterised. In these models, other factors (carryover effects and period effects) are also considered. The mixed models are fitted using the ‘lme4’ package in R software (version 3.6.2). Different models are compared using the Bayesian information criterion (BIC) [35]. Finally, we prefer the model with the lowest BIC.

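### The 80% power assumes one treatment effect shared by all patients, and the pooled analysis is not fixed so as to stay valid if effects differ between patients

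*Protocol article*

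**What the plan says.** The Sample size section takes two figures from a published study of mucus-in-stool VAS: "the standard deviation of self-efficacy was 0.8" and "the difference value of efficacy between the two groups was 0.7". It continues "We assume that there is no difference in efficacy between each patient", then "Assuming a two-sided significance level of 0.05 and power of 80"%, and reports that "the sample size is calculated as 8 (fixed model"). A 20% allowance for loss raises this to 10.

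Other sections point towards effects that differ between patients:

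- The rationale for the N-of-1 design says "Patients need personalised treatment to alleviate prolonged suffering", and Statistical methods plans a separate test for each patient.
- The mixed model covers both cases: a common effect is fixed, and an effect that "varies across different patients, it is a random effect".
- The Discussion, in the abstract and in the main text, anticipates that the herbal treatment will prove effective in patients with UC in remission, which is a statement about a population.

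For pooling, Statistical methods names a paired t test without giving its unit (cycle pairs or patient means). It then adds "Considering the correlated data structure, we also used a mixed model". Among the candidate models, the one with the lowest BIC is preferred.

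**The concern.** The power calculation uses the one scenario in which patients do not differ in their response. A claim about patients in general has to carry the between-patient variance of the effect in its standard error, with degrees of freedom that come from the number of patients and not from the number of cycles. Two separate things are at stake. The first is whether the trial has the stated power for the conclusion it expects to draw. The second is whether the pooled test and its interval are valid for the mean effect: if the cycles of one patient are treated as independent when effects vary, the interval is too narrow. The plan names two pooled analyses, does not say which decides, and lets BIC settle whether the random effect stays in.

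**Working it through.** **Inputs.** From Sample size: difference δ = 0.7, SD σ = 0.8, two-sided α = 0.05, power 80%, 8 analysed and 10 enrolled. From Trial design: k = 3 cycles, so three paired differences per patient. The between-patient SD of the treatment effect, τ, is not in the document beyond the assumption that it is zero. The values 0.2, 0.35, 0.5 and 0.7 are my assumption; the last three run from half of the 0.7 effect to all of it.

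**Reproducing 8.** Read 0.8 as the SD of one period's score. With a common effect and n × k independent pairs, SE = √(2σ²/(nk)).

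- Normal approximation: n = (1.960 + 0.842)² × 2 × 0.64 / (3 × 0.49) = 6.83, so 7.
- Noncentral t: n = 7 gives 77.0% (df nk − 1 = 20) or 75.1% (df n(k − 1) = 14). n = 8, with SE = √(1.28/24) = 0.231, gives 82.7% (df 23) or 81.2% (df 16).

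The smallest n reaching 80% with the t distribution is therefore 8, and 8/0.8 = 10. If 0.8 were the SD of a within-cycle difference, 5 patients would suffice, so that reading does not reproduce the plan.

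**Patient-level power.** For a claim about the mean effect, SE = √((τ² + 2σ²/k)/n) with n − 1 df, where 2σ²/k = 1.28/3 = 0.427. Example at τ = 0.35, n = 8: √((0.1225 + 0.427)/8) = 0.262, giving 63%.

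| τ | SE, n = 8 | Power, 8 completers | Power, 10 completers | Completers for 80% |
|---|---|---|---|---|
| 0 | 0.231 | 74% | 85% | 9 |
| 0.2 | 0.242 | 70% | 82% | 10 |
| 0.35 | 0.262 | 63% | 76% | 11 |
| 0.5 | 0.291 | 55% | 67% | 13 |
| 0.7 | 0.339 | 43% | 54% | 17 |

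The 74% at τ = 0 is not a cost of heterogeneity. The SE is the same as in the fixed model, and only the df fall, to 7. With all 10 patients complete, power stays at or above 80% up to τ of about 0.26.

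**Type I error if all cycle pairs are pooled as independent.** The t test then uses a variance of about (τ² + 2σ²)/(nk), while the true variance is (τ² + 2σ²/k)/n. At τ = 0.5 and n = 8 these are 1.53/24 = 0.064 and 0.677/8 = 0.085, so the test uses an SE of about 0.25 where 0.29 is needed. Simulated rejection rates with the mean effect at zero (400,000 trials per setting, n = 8):

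| τ | All 24 pairs | Patient means |
|---|---|---|
| 0 | 5.0% | 5.0% |
| 0.2 | 5.7% | 5.0% |
| 0.35 | 7.1% | 5.0% |
| 0.5 | 8.8% | 5.0% |
| 0.7 | 11.6% | 5.0% |

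With 10 patients (30 pairs) the all-pairs figures agree to within 0.1 percentage points.

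**Does BIC protect?** I used a simplified version: within-cycle differences, one extra variance parameter, and a penalty based on the number of differences. With 10 patients the random treatment effect was selected in 3%, 6%, 12% and 26% of trials at τ = 0.2, 0.35, 0.5 and 0.7. With 8 patients it was 3%, 6%, 11% and 23%. Type I error after selection, with 10 patients, was 5.6%, 6.7%, 8.0% and 9.5%. In most trials the fixed-effect model is kept and most of the inflation remains.

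**The case against.** The assumption is disclosed: the section states it and labels the result as coming from a fixed model. The analysis section provides a random effect for the other case. The remark on personalised treatment is a general rationale and says nothing about a variance, so the sections are in tension and not in formal contradiction. All of this stands. It does not remove the point, because the expected conclusion is about patients in general and the only power figure given does not apply to it once effects vary.

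A reader might go further and infer that this trial's power is well below 80% and its error rate above 5%. The documents do not support that, for four reasons:

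- No τ is given. At τ = 0.2 the patient-level test has 82% power with 10 completers, and the all-pairs test has 5.7% error. The large effects need τ of half the treatment difference or more.
- The two harms fall on different tests. The all-pairs test that exceeds 5% still rejects in 78% of trials at τ = 0.35 with 8 patients. The patient-level test that loses more power keeps 5%.
- The unit of the pooled t test is inferred. A paired t test on patient means fits the wording, keeps 5% and does not assume equal effects. The cycle-level reading is supported only by the next sentence, which brings in the mixed model because the data are correlated.
- The inflation concerns a zero mean effect with patients varying around it. If no patient has any effect, the all-pairs test keeps 5%.

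An article may also leave the unit of a test to a fuller document. The BIC rule, however, is stated here, and it decides whether the random effect survives.

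**Conclusion.** The point holds in a limited form. The 80% with 8 patients is correct for the fixed model: it requires a common effect, with cycle pairs analysed as independent. It is not the power of the population statement that the Discussion anticipates. For that statement, power with 8 completers is 74% even without heterogeneity, because of the smaller df, and 70% to 43% for τ from 0.2 to 0.7. With 10 completers it is 82% to 54% over the same range. Separately, a t test on all cycle pairs, if that is what is meant, has about 5.7% to 11.6% type I error over that range, and selection by BIC removes little of it. All of these figures rest on 0.8 being the SD of a period score, on complete data from three cycles, and on an assumed τ. They show how sensitive the plan is to its assumption, not what will happen in this trial.

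**What to change.** Before unblinding, name one pooled analysis that decides. Either of these would serve:

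- a mixed model that always keeps a random patient-by-treatment effect, with small-sample df (Kenward-Roger or Satterthwaite); or
- a t test on the patient mean differences, with df equal to the number of patients analysed minus 1 (9 if all 10 complete, 7 if 8 do).

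The two are not interchangeable once there are dropouts or period and carryover terms, so one must be chosen. BIC may still choose among residual covariance structures, but must not remove the random treatment effect. Drop a t test on all cycle pairs, or label it supportive and state its unit.

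In Sample size, keep 10 patients, say that 80% applies only if all patients share one effect, and add the patient-level power over a range of effect SDs: for example, 63% with 8 completers and 76% with 10 at an effect SD of 0.35.

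This needs wording only and no extra patients. The price is a less favourable stated power and somewhat wider intervals. It makes the claim honest but does not restore 80% power if effects vary substantially.

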### Randomisation, treatment allocation, and blinding

The sequence of the test period was randomly assigned within each of three pairs of periods using an SAS random programme. There are two treatment periods in each cycle, the intervention period (A) and the control period (B). Only AB and BA are allowed in each cycle. The random programme will be created by statisticians from the School of Basic Medical Science of GZUCM. According to this, the test drugs will be randomly hand out by the researcher who will not participate in the trial. The prepared research drugs will be delivered, stored, and distributed in the First Affiliated Hospital of GZUCM. Patients and investigators will be blinded to all randomisation and packaging procedures until completion of the trial.

The modified SJZD (or mesalazine) placebo tablets will closely resemble the appearance, odour, and taste of the active modified SJZD granules (mesalazine). Placebos will be packaged in the same way as the active tablets to minimise the risk of breaking the blind.

### Statistical methods

All data will be recorded and collected on the CRFs by the researchers. The data will be input using EpiData 3.0 (EpiData Association, Odense, Denmark). To ensure the accuracy and integrity of the data, double data entry and proofreading will be performed by two independent researchers.

R software (version 3.6.2) will be utilised for the statistical analysis. A *P* value ≤ 0.05 will be considered statistically significant. For the quantitative indicators, the mean and standard deviation or the median and interquartile range will be calculated. Descriptive statistics will be used to summarise the demographic characteristics of the participants, including age, sex, and extent of UC.

For the individual *N*-of-1 trials, paired *t* tests or Wilcoxon signed-rank tests will be used to compare the efficacy (including the VAS for diarrhoea, abdominal pain, mucus in the stool, and bloody purulent stool, as well as all the QOL scores) of modified SJZD with that of mesalazine. For individual patient reports, the VAS for diarrhoea, abdominal pain, mucus in the stool, and bloody purulent stool, as well as all the QOL scores and safety indicators reported, will be described, as will whether the efficacy is within the range of significant improvement.

To synthesise the data from the *N*-of-1 trials from all patients (including the VAS for diarrhoea, abdominal pain, mucus in the stool, and bloody purulent stool, as well as all the QOL scores), a paired *t* test was used for the analysis. Considering the correlated data structure, we also used a mixed model. The equation for the mixed model is as follows [34]:
1$$ {\displaystyle \begin{array}{l}{Y}_i={X}_i{\theta}_i+{\varepsilon}_i\kern0.5em \mathrm{with}\kern0.5em {\varepsilon}_i\sim N\left(0,{\Sigma}_i\right)\\ {}{\theta}_i\sim N\left(\theta, D\right)\end{array}} $$where *Y*_*i*_ = (*Y*_*i1*_, *Y*_*i2*_, …, *Y*_*ij*_) denotes the *i*-th (*i* = 1, 2, …, *n*) subject’s response value for the *j*-th (*j* = 1, 2, …6) period; *θ*_*i*_ follows a multivariate normal distribution with mean *θ* and a covariance matrix *D*. *θ*_*i*_ contains treatment effect (μ_i_) between mesalazine and modified SJZD. When *μ*_*i*_ is same for each patient (*μ*_*i*_ *= μ*), it is a fixed effect. If *μ*_*i*_ varies across different patients, it is a random effect. Some covariance structures for the random error are assumed, including: (1) compound symmetry (common variance across patients with uncorrelated and identically distributed errors), (2) first-order autoregressive, and (3) unstructured: which may be overparameterised. In these models, other factors (carryover effects and period effects) are also considered. The mixed models are fitted using the ‘lme4’ package in R software (version 3.6.2). Different models are compared using the Bayesian information criterion (BIC) [35]. Finally, we prefer the model with the lowest BIC.

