## Methods

### Trial design

Three cycles of *N*-of-1 trials were chosen for the following reasons: (1) *N*-of-1 trials generally involve three or more cycles. Three cycles are the most commonly planned number of treatment cycles [30] and (2) for *N*-of-1 trials, the number of cycles is a variable in the sample size calculation [29]. Different cycles result in different sample sizes. Longer cycles will result in a higher dropout rate.

The *N*-of-1 trials will consist of three cycles, each cycle comprising 8 weeks of an intervention period and 8 weeks of a control period, in a random order. There is no washout period in this study. The protocol conforms to the Standard Protocol Items: CONSORT extension for reporting *N*-of-1 trials (CENT) 2015 [26]. Table 1 shows the schedule of enrolment, interventions, and assessments.

**Table 1 Tab1:** Schedule of enrolment, interventions, and assessments

Time point		Enrolment	Allocation	Cycle1		Cycle2		Cycle3		Close-out
				Weeks1–8	Weeks9–16	Weeks17–24	Weeks25–32	Weeks33–40	Weeks41–48	
Enrolment	Eligibility screen	**X**								
	Informed consent	**X**								
	Allocation		**X**							
Intervention	Modified *Sijunzi* decoction combined with mesalazine placebo or mesalazine combined with modified *Sijunzi* decoction placebo			**X**	**X**	**X**	**X**	**X**	**X**	
Assessment	Laboratory tests	**X**		**X**	**X**	**X**	**X**	**X**	**X**	**X**
	Vital signs	**X**		**X**	**X**	**X**	**X**	**X**	**X**	**X**
	Adverse events			**X**	**X**	**X**	**X**	**X**	**X**	
	VAS (abdominal pain, diarrhoea, bloody stool, mucus stool), stool frequency, SIBDQ, RFIPC, SHS, and TCM syndrome scale	**X**		**X**	**X**	**X**	**X**	**X**	**X**	

*RFIPC* Rating Form of Inflammatory Bowel Disease Patient Concerns*, SHS* Short Health Scale*, SIBDQ* Short Inflammatory disease Patient Concerns, *TCM* traditional Chinese medicine, *VAS* visual analogue scale

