### Outcomes

The primary outcomes for this trial are the changes in the visual analogue scale (VAS) for diarrhoea, abdominal pain, mucus in the stool, and bloody purulent stool. The secondary outcomes will include the TCM syndrome scale, the Short Inflammatory Bowel Disease Questionnaire (SIBDQ), the Rating Form of Inflammatory Bowel Disease Patient Concerns (RFIPC), and the Short Health Scale (SHS). Efficacy indicators for each subject will be observed and recorded before the study and at the end of each period (including week 8, week 16, week 24, week 32, week 40, and week 48).

Patients will be asked to rate their diarrhoea, abdominal pain, mucus in the stool, and bloody purulent stool severity by placing a vertical mark on a 10-mm horizontal VAS. The left and right extremes of the VAS are labelled ‘the lightest’ and ‘the most serious’, respectively.

The (TCM) Traditional Chinese medicine syndrome scale is an efficacy evaluation of six items measuring dampness, stagnancy due to spleen deficiency syndrome: diarrhoea, bloody purulent stool, anorexia, abdominal distension, limb burnout, and disinclination to talk due to mental weariness. Each item is rated from 0 to 3. The higher the scale, the more serious is the dampness stagnancy [11].

The SIBDQ uses 10 items derived from the inflammatory bowel disease questionnaire, which explain 90% of the variance in the SIBDQ for UC patients. The total score ranges from 10 (worst health) to 70 (best health). This gauge of subjective health status or quality of life in patients can be administered and scored quickly and easily [31].

The RFIPC is a self-administered form containing 25 items of concern related to inflammatory bowel disease. Each item is rated from 0 to 100 on a VAS form. The average score of all 25 items is the ‘sum score’. A higher score indicates a higher level of patient anxiety [32].

The SHS is a disease-specific questionnaire consisting of four items measuring four dimensions of health: bowel symptom severity, social functioning in daily life, disease-related worry, and perceptions of general well-being. Item responses are indicated on a 100-mm VAS from 0 to 100. The higher the scale, the more serious are the health concerns [33].

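### With three paired differences per patient, the individual Wilcoxon test cannot reach P ≤ 0.05 and the individual paired t test has about 10–15% power at the planning values

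*Protocol article*

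**What the plan says.** The number of pairs per patient follows from three sections of the protocol article.

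- **Trial design** sets three cycles, "each cycle comprising 8 weeks of an intervention period and 8 weeks of a control period, in a random order".
- **Randomisation, treatment allocation, and blinding** says the order is "randomly assigned within each of three pairs of periods".
- **Outcomes** says efficacy is "observed and recorded before the study and at the end of each period", which means weeks 8, 16, 24, 32, 40 and 48.

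**Statistical methods** then assigns the individual analysis: paired t "tests or Wilcoxon signed-rank tests will be used to compare the efficacy" for the four symptom VAS scores and all quality-of-life scores. The threshold appears earlier in the same section: a P "value ≤ 0.05 will be considered statistically significant". The section sets no separate rule for single patients. It also plans a descriptive report for each patient, and it pools all patients with a paired t test and a mixed model.

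**Sample size** addresses the pooled series only ("Assuming a two-sided significance level of 0.05 and power of 80" per cent). It takes a difference of 0.7 and an SD of 0.8 for the mucus VAS, arrives at 8 patients, and recruits 10. It gives no power for the individual tests.

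**The concern.** One of the two tests named for the individual trials cannot satisfy the plan's own significance rule, whatever the data show. The other will rarely do so at the effect the trial is planned around.

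Personalised treatment is one of the reasons the article gives for the N-of-1 design, and the individual comparison is the analysis that serves it. A significance verdict that is impossible under one test and improbable under the other tells a patient or clinician almost nothing. Where a t test does cross the threshold, the estimate beside it will be inflated, because with 2 degrees of freedom significance usually requires a mean difference well above the true one, an unusually small sample SD, or both.

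**Working it through.** **Inputs.** Three pairs per patient (Trial design; Randomisation), one reading per period (Outcomes), threshold 0.05 (Statistical methods), difference δ = 0.7 and SD 0.8 (Sample size). The article does not say whether 0.8 is the SD of a single period's reading or of the paired difference.

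**Step 1: reproduce the stated sample size.** Take 0.8 as the within-patient SD per period, with k = 3 cycles and a common effect. The variance of the pooled effect is 2 × 0.8² / (3n).

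- Normal approximation: 3n = 2 × 0.64 × (1.960 + 0.842)² / 0.49 = 20.5, so n = 7.
- Noncentral t with 2n df: power 0.751 at n = 7 and 0.812 at n = 8.
- Noncentral t with 3n − 1 df: power 0.770 at n = 7 and 0.827 at n = 8.

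Both t versions give n = 8, and 8 / 0.8 = 10. The stated 8 and 10 are reproduced. Reading 0.8 as the SD of the differences gives 4 (normal) or 6 (t with n − 1 df), a poorer match. The per-period reading is therefore used first below, with the other as the alternative.

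**Step 2: individual Wilcoxon test.** Three non-zero differences have 2³ = 8 equally likely sign patterns under the null. The most extreme two-sided P is 2/8 = 0.25. Five pairs would give 2/32 = 0.0625 and six pairs 2/64 = 0.031, so at least six pairs are needed. If software switches to a normal approximation because of ties, the smallest P with three non-zero differences is still about 0.15 with continuity correction and 0.08 without.

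**Step 3: individual paired t test.** There are 3 − 1 = 2 df and the critical value is 4.30. The noncentrality is δ / (SD of difference / √3).

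| | 0.8 is per-period SD | 0.8 is SD of differences |
|---|---|---|
| SD of difference | 0.8 × √2 = 1.13 | 0.8 |
| Noncentrality | 0.7 / 0.653 = 1.07 | 0.7 / 0.462 = 1.52 |
| Power | 10.2% | 15.1% |
| Power by simulation (400,000 runs) | 10.1% | 15.1% |
| Non-significant patients, per outcome | about 90% | about 85% |
| True difference needed for 80% power with 3 pairs | 3.7 | 2.6 |
| Pairs needed for 80% power at 0.7 | 23 | 13 |
| 95% interval half-width if the sample SD equals the true SD | 4.30 × 0.653 = 2.8 | 4.30 × 0.462 = 2.0 |

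The difference needed for 80% power is 3.7 / 0.7 = 5.3 or 2.6 / 0.7 = 3.7 times the planned one.

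**Step 4: size of the significant results.** In 2,000,000 simulated patients with a true difference of 0.7, those significant by t test had a mean absolute difference of 1.35 (1.09 on the alternative reading). That is 1.9 (1.6) times the truth.

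**Step 5: what pooling the residual variance buys.** With 8 to 10 patients there are 16 to 20 residual df (2 per patient), and the critical value falls from 4.30 to 2.12–2.09. The half-width becomes 2.12 × 0.653 = 1.4 (1.0 on the alternative reading), about half the stand-alone width. It still exceeds 0.7.

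**The case against.** The strongest reply is that the trial does not rest on these tests. The objective is a comparison through a series of trials, the sample size is set for that series and reproduces, and the pooled paired t test and mixed model are separate analyses. Personalised treatment is only one of several reasons given for the design. All of this stands. It limits the defect to the individual analyses and lowers its severity, but it does not make the individual Wilcoxon test able to reject.

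Two stronger readings are tempting, and the article supports neither.

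- A reader might infer that every patient is bound to be non-significant whatever the truth. That holds only if Wilcoxon is used. The plan offers the t test as the alternative, and at the planned effect about 1.0 to 1.5 patients in 10 would be significant on a given outcome. The number would be higher where a patient's own effect is larger.
- A reader might infer that a non-significant patient will be declared to show no difference between treatments. No section says so. The individual reports are described, the phrase about significant improvement could mean a clinical threshold rather than a P value, and the Discussion promises cautious interpretation.

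It can also be said that the mixed model already allows a treatment effect that varies by patient. That helps only in part. The model is assigned to the synthesis across patients, and choosing the lowest BIC may select the version with a common effect, which gives no individual estimates.

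Finally, 0.7 and 0.8 are planning values for one outcome from one cited study. Power for the other VAS items and the quality-of-life scores cannot be derived from the article. The Wilcoxon limit depends on none of these values.

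**Conclusion.** Wrong as written, and should be fixed. The individual Wilcoxon test cannot give an exact two-sided P below 0.25 and so can never meet the stated rule. This follows from the number of pairs alone. The individual paired t test has about 10% power at the mucus VAS planning values if 0.8 is the per-period SD, and 15% if it is the SD of the differences. Both figures assume normally distributed, independent differences and all three cycles completed; a patient who completes fewer has less information still.

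A later analysis plan could not rescue the Wilcoxon option by adding detail, because the pairs, the tests and the threshold are all fixed here. The pooled paired t test, the mixed model and the sample size are untouched by this point.

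**What to change.** In Statistical methods, remove the individual Wilcoxon test and state that the P ≤ 0.05 rule does not apply to single patients. For each patient and outcome, report:

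1. the three paired differences;
2. their mean with a 95% interval, preferably using the residual variance pooled across patients (which assumes a common within-patient variance);
3. a statement that non-significance, or an interval that includes zero, is not evidence of equal effect in that patient.

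A shrunken individual estimate with its interval may be added from a mixed model whose random treatment effect is specified in advance and does not depend on BIC selection. It should not be the core of the report. With about 8 to 10 patients the between-patient variance is poorly estimated. Under the sample size section's own assumption of equal efficacy in all patients, that variance is zero and every shrunken estimate collapses to the pooled mean.

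The cost is a change of wording and a little more analysis work, with no change to design, visits or sample size. The downside is that individual results become estimates with wide intervals instead of P values.
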